## Methods

### Trial design

This will be a pragmatic, controlled intervention study with random allocation of three parallel training conditions (allocation ratio 1:1:1), using single-blinded outcome assessments. Intervention conditions are allocated at the fitness-center level, such that all exercise professionals within a given club are exposed to the same training condition. Although outcomes are measured at the individual member level, the primary unit of inference is the fitness center, with individual-level data used to characterize attendance trajectories and variability over time within each condition. The study will be conducted between September 2025 and August 2026. The training program will be applied in three health clubs belonging to the same company, to most of the exercise professionals employed at these clubs (> 80%), and at the beginning of the club season. Although all participating fitness centers belong to the same company, they operate with independent professional teams and geographically separated facilities. No systematic staff movement between the centers is expected during the intervention period. In addition, club managers were asked to avoid sharing the specific contents of the training sessions across centers throughout the implementation period. Training sessions were delivered independently within each fitness center according to the allocated condition.

Shorter content and operational/contextual strategies will be reinforced individually at approximately three-month intervals. For one year, all new club memberships and dropouts will be recorded. Moreover, approximately 39 exercisers per arm will be recruited to be monitored throughout the entire period, allowing the close assessment of changes in behavioral and motivational variables of interest. Considering that the clubs are business entities, the successful completion of the planned study will require close cooperation of the researchers with the managers of the fitness centers in planning the recruitment, advertising the study, and choosing the most appropriate time to intervene with each professional individually. The SPIRIT guidelines, as proposed by Chan et al. (2025), were followed for the development of the present protocol. The trial was preregistered on ClinicalTrials.gov with the ID number NCT07156240.

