### Sample size

Sample size determination follows SPIRIT (Chan et al., 2025) guidance for pragmatic interventions in which traditional power calculations are constrained by design features. As such, considerations were made while considering the nature of the intervention, the fitness-center–level allocation of training conditions, and the longitudinal structure of the primary outcome. Given that only three centers are included, formal power calculations for between-condition hypothesis testing based on individual-level randomization are not appropriate. Instead, sample size adequacy is primarily related to the large number of individual observations and repeated measurements, which support the longitudinal estimation of attendance trajectories over time within the constraints of the present pragmatic design.

For the primary outcome (attendance), all eligible members of the participating fitness centers will be included in the analyses at three, six, nine, and 12 months, although the focus will be given to those enrolled after September 1, 2025. Each participating fitness center has more than 2,000 enrolled members at any given time, and historical records indicate that approximately 200 new members typically enroll in each club during the month of September. This provides a high-density longitudinal dataset, with multiple repeated observations per individual and sufficient sample size in each intervention condition to support longitudinal mixed-effects modeling of attendance trajectories.

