### Statistical methods

Preliminary analyses will be conducted prior to all statistical procedures to examine data quality, missingness patterns, and identify potential violations of statistical assumptions. All analyses are planned to be performed using SPSS v.27.0 (IBM, Co.). The primary outcome of the study is attendance, which will be analyzed both for all fitness center members and separately for those who joined the clubs after the commencement of the study (i.e., after September 1, 2025). Attendance will be operationalized as the individual’s mean weekly attendance within each three-month interval and assessed at four time points during the 12 months of the study (three, six, nine, and twelve months). Primary analyses of attendance will be conducted using linear mixed-effects models (LMMs), with time specified as a within-subject factor and individuals treated as random effects to account for repeated observations. Intervention condition (control, SDT-based training, and hedonic-based training), time, and their interaction will be included as fixed effects, with age and sex included as covariates. These models will be used to characterize and descriptively compare attendance trajectories over time across intervention conditions, with emphasis on the magnitude and direction of longitudinal patterns rather than on individual-level causal inference. Primary analyses will follow an intention-to-treat principle adapted to the cluster-allocated design, such that all eligible individuals are analyzed according to their fitness center’s assigned condition, regardless of attendance patterns or dropout. Linear mixed-effects models were selected because they incorporate all available longitudinal observations under a missing-at-random assumption without requiring imputation.

Because intervention allocation occurs at the fitness-center level and each condition is implemented in a single center, cluster-level variance and intraclass correlation coefficients cannot be estimated independently of condition-related effects. Accordingly, comparisons across intervention conditions are considered exploratory and descriptive in nature. For complementary descriptive purposes, 3 (Condition) × 4 (Time Points) split-plot ANOVAs may be conducted to summarize overall patterns of longitudinal change in attendance. Results from these analyses will be interpreted descriptively, given that intervention conditions are implemented at the fitness-center level.

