Secondary outcomes include dropout and motivational variables. Dropout (membership cancellation) will be examined using administrative records from all members enrolling after September 1, 2025. Dropout rates will be summarized at three-month intervals, and time-to-event analyses will be used to describe adherence patterns over the 12-month period. Percentage attrition rates will be reported descriptively, and Kaplan–Meier survival curves will be used to illustrate the timing of dropout across conditions. Participants who remain actively enrolled at the end of the observation period will be treated as censored observations at their last available follow-up time point. Motivational and behavioral variables will be analyzed in the longitudinal subsample of participants. Changes over time in these variables (baseline, six, and twelve months) will be examined using linear mixed-effects models, with time specified as a within-subject factor and participants treated as random effects. Intervention condition, time, and their interaction will be included as fixed effects, with age and sex entered as covariates. Given the limited number of repeated measurements, models will be specified with a parsimonious random-effects structure. For consistency with prior literature and ease of interpretation, complementary 3 (Condition) × 3 (Time Points) split-plot ANOVAs may also be conducted, with results interpreted descriptively. Effect sizes will be reported as model-based estimates of change over time (e.g., differences in attendance slopes and estimated marginal means), with 95% confidence intervals. Additional control, complementary, and exploratory analyses are anticipated, particularly within ancillary studies.

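### The planned 95% confidence intervals for between-condition differences leave out club variance, because each condition is one club and only individuals are random

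*Protocol article*

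**What the plan says.** All statements are in the protocol article.

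- **Trial design:** there are "three parallel training conditions (allocation ratio 1:1:1"), allocated by club, and "the primary unit of inference is the fitness center".
- **Statistical methods, primary model:** condition, time and their interaction are fixed effects, age and sex are covariates, and the random part consists of "individuals treated as random effects to account for repeated observations". There is no club term.
- **Statistical methods, limits:** the section concedes that, because "each condition is implemented in a single center, cluster-level variance and intraclass correlation coefficients cannot be estimated independently of condition-related effects", comparisons across conditions are exploratory and descriptive.
- **Statistical methods, reporting:** effect sizes are to be model-based estimates of change over time, with the examples "differences in attendance slopes and estimated marginal means), with 95% confidence intervals". Nothing says what the intervals condition on or leave out.
- **Sample size:** the section declines to calculate power for contrasts between conditions, since there are only three clubs. What it offers in place of such a calculation is the claim that "sample size adequacy is primarily related to the large number of individual observations and repeated measurements".
- **Objectives:** the hypotheses are directional between conditions: either training better than control on attendance trajectories, and hedonic training with higher attendance than SDT training.

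**The concern.** The plan names the club as the unit of inference and accepts that club variance cannot be estimated. It then attaches to its effect sizes an interval whose width comes only from variation among and within members. For a contrast between conditions, that interval answers a narrower question: how precisely the mean difference between the members of these particular clubs is known. It does not say how far two clubs would differ by chance if neither training had any effect.

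The primary hypotheses concern the training. A reader checking them will look at whether the interval excludes zero, and an ordinary difference between two clubs can produce that result. Adding members narrows the interval while the omitted club component stays the same, so the largest analysis (all members) looks the most precise and is the most exposed.

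**Working it through.** **The plan's own figure.** No precision or power figure is given for between-condition attendance differences, so there is none to reproduce. The one calculated sample size, 53 completers in the motivational subsample, does reproduce. A within-factor repeated-measures ANOVA with f = 0.20, three measurements, r = 0.70, epsilon = 0.70 and alpha = 0.05 has power 0.953 at N = 53. Inflating gives 53/0.45 = 117.8, against about 117 stated. That calculation concerns change over time within participants and gives no support to a between-condition interval.

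**Degrees of freedom.** 3 clubs − 3 conditions = 0. The trial's data cannot supply a club-level standard error for a condition contrast.

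**What the interval omits (difference in level between two clubs, n members each, one summary value per member).**

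- Variance used by the planned model: 2σ_w²/n.
- Variance including clubs: 2σ_w²/n + 2σ_club².

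The first goes to zero as n grows; the second does not fall below 2σ_club². With the usual design effect DE = 1 + (n − 1) × ICC, the chance that a nominal 95% interval excludes zero when there is no true effect is 2 × [1 − Φ(1.96/√DE)].

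**Inputs.** n = 200 is the approximate number of new members per club in September, and n = 2,000 is the stated lower bound on enrolled members per club (both from Sample size). The ICC is not in the documents; 0.001 to 0.05 is an assumed range.

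| n per club | Assumed ICC | DE | 1.96/√DE | Excludes zero, no true effect |
|---|---|---|---|---|
| 200 | 0.001 | 1.20 | 1.79 | 7% |
| 200 | 0.01 | 2.99 | 1.13 | 26% |
| 200 | 0.05 | 10.95 | 0.59 | 55% |
| 2,000 | 0.001 | 3.00 | 1.13 | 26% |
| 2,000 | 0.01 | 20.99 | 0.43 | 67% |
| 2,000 | 0.05 | 100.95 | 0.20 | 85% |

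**Cross-check.** Since condition and club coincide, the fitted model sees only the within-club variance. The exact ratio of standard errors is then √[1 + n × ICC/(1 − ICC)]. At n = 200 and ICC 0.05 it is 3.40, giving 56% instead of 55%. At n = 2,000 and ICC 0.01 it is 4.6, giving 67%. The two forms agree to within about one percentage point throughout the table.

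**Slopes.** A stable difference in level between clubs cancels from a difference in slopes. What is omitted there is the variance of the club-by-time effect, which is equally confounded with condition and equally inestimable. The table gives no size for it.

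**The case against.** The strongest reply is that the plan is already candid. It states that "cluster-level variance and intraclass correlation coefficients cannot be estimated independently of condition-related effects", calls comparisons across conditions descriptive, rejects formal between-condition power calculations, and sets no p-value threshold or decision rule for a between-condition contrast. All of that stands and deserves credit. But a 95% confidence interval is itself a statement of uncertainty, and the descriptive label does not change its width or tell the reader what it leaves out.

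A second reply is that the reporting sentence concerns change over time, so the estimated marginal means may be within-condition values, for which an interval is reasonable. That reading is possible for the means. It fits slope differences poorly: in a model with a condition-by-time interaction, used to compare trajectories across conditions, a difference in slopes is most naturally between conditions.

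A reader might also infer four stronger things that the documents do not support:

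- **That the intervals are far too narrow whatever the setting.** With 200 members and an ICC of 0.001 the false-exclusion rate is about 7%. New members enrol until August 2026, however, so the analysed number will exceed the September figure.
- **That the tabulated percentages are error rates for slope differences.** They apply to level contrasts only.
- **That the plan intends to declare its hypotheses confirmed from these intervals.** It states no such step.
- **That the Sample size section claims precision for the training effect.** Its sufficiency claim is limited to mixed-effects modelling of trajectories, within the constraints of the design.

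**Conclusion.** The point holds in this form: any between-condition 95% interval from the planned model omits club variance (for slopes, club-by-time variance) and cannot be read as uncertainty about the training effect. This follows from the document's own statements and needs no assumed ICC.

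The size does need one. For level or marginal-mean contrasts, and for ICCs from 0.001 to 0.05, false exclusion of zero runs from about 7% to 55% at 200 members per club and from about 26% to 85% at 2,000, against a nominal 5%. The all-member analysis is thus affected even at the smallest ICC considered, while the new-member analysis depends on the ICC and on how many join over the year. The size for slope differences is unknown. Intervals for change over time within one club are not affected when read as describing that club.

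**What to change.** In Statistical methods, restrict model-based 95% intervals to change over time within each club. For between-condition differences, choose one of two options:

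1. Report point estimates only, without individual-level intervals or p-values.
2. Keep the intervals, label them as conditional on these three clubs and excluding club variance (club-by-time variance for slopes), and add a sensitivity range over stated ICCs, for example 0.001 to 0.05 for level contrasts, marked as assumption-based.

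Under either option, show the one-year pre-intervention club attendance already listed under Outcomes, as an indication of how far the clubs differ without the training.

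In Sample size, the trajectory-modelling statement can stay. Add one sentence saying that each condition has one club, so a larger number of members adds no information on the between-condition effect.

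The cost is wording and table layout, with no new data. The stated precision of the between-condition comparisons becomes less favourable.

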### Ethics and dissemination

The present trial is registered under the ID number NCT07156240. Ethics approval was obtained from the institutional ethics committee of the university of the primary investigator, prior to the commencement of the study. All procedures will be conducted in accordance with international ethical standards for research involving human participants (World Medical Association, 2013). Club manager authorization and signed informed consent will be obtained from professionals and participants during the recruitment phase by two of the researchers. All will retain the right to withdraw from the study at any point without any negative consequences. Study enrollment and participation will be suspended if any major adverse events are identified, following international guidelines (Medical Research Council, 2017), although, given the nature of the study, no adverse events are expected. Should protocol amendments become necessary, additional approval will be sought from the institutional ethics committee, and participants and clubs will be informed of any changes and their potential implications. The leading author will periodically monitor the trial development.

The results of this trial will be published in peer-reviewed scientific journals. Preliminary, intermediate, or secondary findings may also be presented at national or international scientific conferences. Baseline data will not be analyzed until the intervention period has concluded. The final, coded, and anonymized dataset will be managed by the primary investigator [name]. Authorship will be determined in accordance with the criteria established by the International Committee of Medical Journal Editors.

## Data Availability

The raw data supporting the conclusions of this article will be made available by the authors, without undue reservation.
